## 7.4 Immunogenicity Analyses

The primary immunogenicity analyses will be based upon the subjects who received at least one dose of study vaccine and were enrolled in one of the three immunogenicity cohorts. No imputation for missing data will be performed. Data will be transformed as appropriate prior to analysis.

### 7.4.1 Intracellular Cytokine Staining Assay

The primary variables of interest for assessment of immune response to MVA85A/AERAS-485 will be the percentage of CD4 and CD8 T cells that produce any one of three cytokines (IFN- $\gamma$ , TNF- $\alpha$ , or IL-2) or any combination of the three cytokines simultaneously following stimulation with peptide pools containing the entire amino acid sequence of Ag85A. Response will be measured by flow cytometry in the intracellular cytokine staining (ICS) assay.

Descriptive statistics will be used to summarize percentage CD4 and CD8 T cell response by treatment group and stimulation antigen (Ag85A), for all subjects in the ICS immunogenicity cohort. Summaries will include the assessment of response at all pre- and post-vaccination immunology time points, as well as change from pre-vaccination to each post-vaccination time point. MVA85A/AERAS-485 immune response will be compared with placebo across all post-immunization time points using a linear model. The model will include time, treatment group, and appropriate interaction terms, and selection of an appropriate covariance structure for the multiple response measures. If T cell response is not normally distributed, appropriate transformations or an alternative model (e.g., area under the curve (AUC) as the measure of immune response) will be explored. Individual models will be prepared by stimulation antigen for CD4 and CD8 T cell response.

The area under the curve (AUC) and associated 95% confidence interval will be used to summarize the immune response by treatment group. Area under the curve will be calculated using the trapezoidal rule, from Study Day 0 across all available post-vaccination time points. An exploratory comparison of the mean AUC for MVA85A/AERAS-485 and control will be performed using the two-sample test.

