**Table 3 Infant Schedule of Evaluations and Treatments Study Day -84 to Study Day 84 for the ICS immunogenicity Cohort**

| Study Day              | -84a | -35a | -7a | 0   | 7   | 28  | 84  |
|-------------------------------|------------------------|------------------------|-----------------------|------------|------------|------------|------------|
| Minimum Age (Days)     | 42              | 91              | 119            | 126 | 133 | 154 | 210 |
| Written Informed Consent      | X                      |                        |                       |            |            |            |            |
| Verify Eligibility Criteria   |                        |                        |                       | X          |            |            |            |
| Medical History               |                        | X                      |                       |            |            |            |            |
| Physical Examination          |                        | X                      |                       |            |            |            |            |
| HIV-1                         |                        | 3                      |                       |            |            |            |            |
| Vital Signs                   |                        |                        |                       | X          | X          | X          | X          |
| Weight                        |                        | X                      |                       | X          | X          | X          | X          |
| Injection Site Photograph     |                        |                        |                       | X          |            |            |            |
| Study Vaccine Administration  |                        |                        |                       | X          |            |            |            |
| QuantiFERON (Gold in tube)    |                        | 3                      |                       |            |            |            |            |
| Immunology Samples            |                        |                        | 8                     |            |            | 8          |            |

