| Solicited Adverse events      |                        |                        |                       | X          | X          |            |            |
| Assess Adverse Events         |                        |                        |                       | X          | X          | X          |            |
| Serious Adverse Event Reports |                        |                        |                       | X          | X          | X          | X          |
| Site of Injection Examination |                        |                        |                       | X          | X          | X          |            |
| Blood volume (mL) per visit   |                        | 6                      | 8                     |            |            | 8          |            |

a Written informed consent must be obtained prior to initiation of study screening activities and may be obtained prior to Day -84. Medical history/physical exams and blood collection for HIV-1 and QuantiFERON testing must be completed within 35 days prior to Study Day 0; blood collections for baseline immunology must be completed within 7 days prior to randomization.

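### The ICS repeated-measures model and the AUC from Day 0 in Section 7.4.1 do not fit a schedule with one pre- and one post-vaccination immunology sample

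*Protocol*

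**What the plan says.** Protocol Section 7.4.1 sets out the main ICS comparison: "MVA85A/AERAS-485 immune response will be compared with placebo across all post-immunization time points using a linear model". It then gives the terms: "The model will include time, treatment group, and appropriate interaction terms, and selection of an appropriate covariance structure for the multiple response measures". If responses are not normally distributed, a transformation or "an alternative model (e.g., area under the curve (AUC) as the measure of immune response) will be explored".

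The AUC, with a 95% confidence interval, is also a planned summary of response by arm. Its definition is: "Area under the curve will be calculated using the trapezoidal rule, from Study Day 0 across all available post-vaccination time points". The associated test is given as: "An exploratory comparison of the mean AUC for MVA85A/AERAS-485 and control will be performed using the two-sample test".

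The schedule in Section 3.1 gives each immunogenicity cohort two immunology draws:

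- ELISPOT (Table 2): the Day -7 column and Day 7.
- ICS (Table 3): the Day -7 column and Day 28.
- Whole blood (Table 4): the Day -7 column and Day 28.

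The Day 0 immunology cell is empty in all three tables. Their footnotes say of the first draw that "blood collections for baseline immunology must be completed within 7 days prior to randomization". Section 7.4 rules out imputation of missing data. Sections 7.4.2 and 7.4.3 allow, but do not require, the Section 7.4.1 analyses for ELISPOT and whole blood.

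**The concern.** The analysis text reads as if it were written for several post-vaccination samples and a Day 0 sample. The schedule supplies neither. Two things follow.

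First, the ICS model has time, interactions and a covariance structure, but only one post-vaccination occasion to apply them to. Second, the AUC starts from a day on which nothing is drawn, and the text does not say whether the pre-vaccination sample takes that place or whether baseline is subtracted.

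At stake is the ICS comparison, in a cohort of 50 to 60 infants (25 to 30 per arm). Someone has to depart from the written text to analyse it. If that choice is left until after unblinding it becomes post hoc, and one natural way of completing the AUC is less sensitive than comparing the post-vaccination value directly.

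**Working it through.** The protocol states no effect size, SD, correlation or power for any immunogenicity cohort, so there is no figure of its own to reproduce.

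**Model.** With one post-vaccination occasion, time has a single level. Its main effect, the time-by-treatment term and any within-infant covariance drop out, leaving a two-arm comparison at that visit. If baseline is entered as a second response, all these terms can be estimated, and the interaction is the difference in mean change.

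**AUC.** Let Y0 be the pre-vaccination value, placed at Day 0, and YD the value at Day D.

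- AUC = D × (Y0 + YD)/2.
- Randomization makes the expected baseline difference zero. With vaccine effect delta on YD, the mean AUC difference is D × delta/2: 3.5 delta for D = 7, and 14 delta for D = 28. Divided by D, it is delta/2 in both cases.
- Let r = SD(Y0)/SD(YD) and rho their correlation. Relative to the post value alone, the standardised effect is multiplied by 1/sqrt(1 + r² + 2 r rho) for the AUC, by 1/sqrt(1 + r² − 2 r rho) for the change score, and by 1/sqrt(1 − rho²) for ANCOVA.

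**Assumed inputs.** 30 per arm (top of the protocol's range), two-sided 0.05, and delta chosen so that the post value alone has 80% power. That gives delta = 0.723 SD, since 0.723 × sqrt(30/2) = 2.80 and 2.80 − 1.96 = 0.84, the 80% point of the normal distribution. The values of r and rho are illustrative.

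Worked case, equal SDs and rho = 0.5: the AUC multiplier is 1/sqrt(3) = 0.577, so 2.80 × 0.577 = 1.62, which is 0.34 below 1.96, giving 37% power. For ANCOVA, 2.80/sqrt(0.75) = 3.23, giving 90%.

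| rho | AUC, r = 1 | AUC, r = 0.5 | AUC, r = 0.25 | ANCOVA |
|---|---|---|---|---|
| 0 | 51% | 71% | 78% | 80% |
| 0.3 | 41% | 61% | 72% | 84% |
| 0.5 | 37% | 56% | 69% | 90% |
| 0.7 | 33% | 52% | 65% | 97.5% |
| 0.9 | 30% | 48% | 62% | about 100% |

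A simulation (20,000 trials, t-test, equal SDs) gave AUC power of 50%, 35% and 31% at rho 0, 0.5 and 0.7, against 79% for the post value alone. The time-averaged AUC difference was 0.50 delta each time.

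If only the vaccine arm's post-vaccination SD rises, to 2, 3 or 5 times baseline, AUC power is 66%, 73% and 77% at rho 0, and 51%, 60% and 69% at rho 0.5.

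A baseline-subtracted AUC is D × (YD − Y0)/2, that is, the change score times D/2. With equal SDs its power is 51%, 80% and 95% at rho 0, 0.5 and 0.7.

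At 25 per arm, with delta reset to keep 80% on the post value, the percentages are the same.

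**The case against.** The strongest reply is that this is loose wording with little consequence. Much of that stands.

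- The AUC test is labelled exploratory, and the linear model is the main comparison. This stands for the test. But the AUC is also a committed summary and the named fallback for non-normal data.
- Sections 7.4.2 and 7.4.3 commit only to descriptive summaries. This stands. A reader might infer that three secondary objectives depend on these methods; the documents tie only the ICS objective to them.
- A reader might infer that the model cannot be fitted at all. That goes too far: it can be fitted with baseline as a second response, and the Study Abstract allows a mixed model or other suitable regression. Section 7.4.1 nevertheless describes the comparison as one across post-immunization times.
- The missing Day 0 sample may be a matter of labelling. Section 7.4.5 reports a Day 0 QuantiFERON result although that blood is drawn at screening, so the pre-vaccination immunology sample may be what is meant. This is plausible, but it is not stated.
- A reader might infer that halving the difference itself costs power, or that a large loss is certain. Neither follows. Halving changes the scale only. The loss comes from baseline variability, and at r = 0.25 with rho = 0 it is 2 percentage points. The protocol claims no immunogenicity power that could be breached.
- Baseline is already used, because change from pre-vaccination is summarised for ICS and ELISPOT. This stands for the summaries, but it does not settle the model or the AUC.
- Covariance structure and baseline handling usually belong in the statistical analysis plan. This is true. But the protocol itself fixes time terms and a start day that its tables do not support, so a later plan would have to depart from it.

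**Conclusion.** The mismatch between Section 7.4.1 and Tables 2 to 4 is real and should be reconciled. It bears chiefly on the ICS comparison, and on ELISPOT and whole blood only if the optional analyses are run. The safety and tuberculosis efficacy analyses are not affected.

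The model has no post-vaccination time factor unless baseline becomes a response. The AUC is undefined on a strict reading. If the unsubtracted baseline is used at Day 0, the AUC has less power than the post-vaccination value alone in every case computed: from about 78% (baseline SD one quarter of post, rho 0) to 30% (equal SDs, rho 0.9), against 80%. At equal SDs it is 51% at rho 0 and 37% at rho 0.5, where ANCOVA has 80% and 90%. These figures rest on the assumed 30 per arm, two-sided 0.05 and 80% starting power, and on SD ratios and correlations that the protocol does not supply. They show a range of possible loss and are not an estimate for this trial.

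**What to change.** In Section 7.4.1, replace the repeated-measures model with an ANCOVA of the single post-vaccination response, transformed as needed, on treatment, with the pre-vaccination value as covariate. State that the sample drawn within 7 days before randomization is the baseline.

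Drop the AUC as summary, fallback and test, or redefine it as baseline-subtracted. With two samples, the redefined AUC carries the same information as the change from baseline.

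Where Sections 7.4.2 and 7.4.3 draw on these methods, the same wording should apply. The Study Abstract already permits this and needs no change.

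The cost is protocol and analysis-plan wording, to be settled before unblinding. Both samples are already scheduled, so no extra blood or data are needed.

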### 7.4.2 ELISPOT

An *ex vivo* IFN $\gamma$  ELISPOT assay will be used to assess specific T cell responses to antigen 85A and other mycobacterial antigens. Descriptive statistics will be used to summarize T cell responses by treatment group and stimulation antigen, for all subjects in the Elispot immunogenicity cohort. Summaries will include the assessment of response at all pre- and post-vaccination immunology time points, as well as change from pre-vaccination to each post-vaccination time point. Additional analyses as described for the ICS assay in Section 7.4.1 may also be presented.

### **7.4.3 Whole Blood Assay**

Concentrations of Th-1 (including IFN-gamma) and Th-2 cytokines will be obtained from supernatants of whole blood cultures stimulated with mycobacterial antigens, for all subjects in the whole blood assay cohort. Cytokine concentrations will be determined with standardized quantitative methods such as ELISA or Multiplex. Cytokine levels at pre and post vaccination time points will be calculated by applying a cytokine standard. Results will be summarized using descriptive statistics at each time point. Additional analyses as described for the ICS assay in Section 7.4.1 may also be presented.

### **7.4.4 Correlates of Protection**

Investigations for determining correlates of immune protection to tuberculosis are ongoing and the technical specifications for the assays are unknown at this time. Decisions on the technical aspects for completing the analysis of correlates of immune protection for this study will be made before the study is unblinded. Further information on the planned analysis will be provided in a separate analytic plan, when available.

### **7.4.5 QuantiFERON conversion rate**

QuantiFERON®-TB Gold test results at Study Day 0, at Study Day 336 and at the last clinic visit, and will be summarized by number (percentage) of positive responses by treatment group and by study group. Cross-tabulation of the number of subjects with a negative QuantiFERON with subsequent conversion to a positive result post vaccination will be summarized by treatment group and by study group. The number (percentage) of subjects with on-study QuantiFERON conversion will also be summarized for those with and without a diagnosis of TB disease during the study, by time point, treatment group, study group, and for all subjects in the safety population.

### **7.4.6 Gene Expression**

The innate immune response to vaccination will be examined as an exploratory objective in this study. A sequentially-enrolled subset of up to 100 randomized subjects will be analyzed using gene expression and transcriptional profile of blood collected at Study Day 1 post-vaccination. Immune response for these subjects will be analyzed using microarray analysis. Analytic techniques will be summarized in a separate analysis plan. The sample size of 100 infants has been selected for an initial review of immune response using these techniques, rather than for statistical reasons. Enrollment into this subset will be performed across study groups, with timing of enrollment contingent on order of completion of screening and consent for this additional evaluation; as a result, the number of subjects in the subset may not be equally allocated between MVA85A/AERAS-485 and control groups.

## **7.5 Safety Analyses**

Safety analyses will be performed using the safety population as defined in Section 7.1.

Summaries of adverse events will be presented for all subjects. Analysis of clinical laboratory results and unblinded safety review following completion of the Study Day 84 time point will be presented based on the study vaccine Safety Cohort (Study Group 1).

### **7.5.1 Adverse Events**

The primary variable for evaluation of the safety of MVA85A/AERAS-485 will be the number and percentage of solicited and unsolicited adverse events (including SAEs) recorded post-vaccination, by MedDRA system organ class (SOC), preferred term, study group, and treatment group.

The number (percentage) of subjects with adverse events occurring within the post-vaccination adverse event reporting period will also be summarized. Additional summaries will include presentations by adverse event reporting period, by severity, and by relationship to study vaccine. Each subject will be counted once per term at the greatest severity or most related state recorded for that term.

Separate summaries for the number (percentage) of subjects with solicited adverse events (injection site reactions and general symptoms) will also be presented. Solicited adverse events will also be summarized by severity; each subject will be counted once per term at the greatest severity recorded for that term.

Serious adverse events (SAEs) will be recorded through the end of study for all subjects. Listings will be provided for all subjects with serious adverse events. Listings will also be provided for all subjects who have discontinued prematurely due to an adverse event.

The number (percentage) of subjects in the Safety cohort with post-vaccination clinical laboratory values recorded as newly abnormal following study vaccination and meeting toxicity mild criteria (Grade 1) or above as specified in the Aeras Pediatric Toxicity Table (Appendix C) will be tabulated at each post-vaccination time point and overall. Clinical laboratory abnormalities will also be reported as adverse events and will be included in the summary of adverse events.

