## ANALYSIS OF PRIMARY OBJECTIVE

The safety profile of the treatment groups will be described. Listings will be provided for all subjects with serious adverse events (SAEs). All subjects who receive study vaccine will be included in the analysis and presentation of adverse events; additional analyses for the safety cohort will also be provided to evaluate clinical safety laboratory results. Adverse events will be summarized by treatment group, by study cohort, and for all subjects. Adverse events will also be summarized by severity and by relationship to study vaccine, by treatment group, study cohort, and for all subjects. Adverse events and clinically relevant laboratory results for the safety cohort will be summarized to examine the relationship between treatment group and key safety endpoints including number (percentage) of solicited and spontaneous adverse events, rates of reactogenicity, and number (percentage) of subjects with newly abnormal post-vaccination laboratory values based on predefined neonatal toxicity criteria.

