### 3.5.2.1 Abnormal Clinical Laboratory Test Results

Results from clinical laboratory tests obtained on the study must be reviewed by the investigator (or a designee who is a medically qualified study team member) within 72 hours of receiving the results to determine if abnormalities exist. If the laboratory value is abnormal, it must be reported as an adverse event and repeated promptly to demonstrate resolution. Additional laboratory tests may be performed if the investigator deems them to be necessary to fully evaluate an adverse event. In the event that the investigator elects to order non-protocol-specified laboratory tests, the investigator must record the rationale for the tests and a determination of clinical significance of the result in the source documents. The investigator must keep the medical monitor informed of adverse events of clinical significance.

Abnormal results and findings will be discussed with the infant's parents/guardians, or the infant will be referred for follow-up with their healthcare provider if necessary.

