### 5.3 Definition of Adverse Event

An adverse event (AE) is defined as any unanticipated problem involving risks to study participants or others. An adverse event, therefore, can be any unfavorable or unintended sign, symptom, disease, syndrome, abnormal laboratory finding, or concurrent illness that

emerges or worsens relative to the infant's pretreatment baseline, whether or not it is considered to be related to the medicinal product.

All conditions that exist prior to administration of the study vaccine (pre-existing conditions) will be recorded in the infant's medical history to establish baseline. Day-to-day fluctuations in pre-existing conditions that do not represent a clinically significant change in the infant's status will not necessarily be reported as adverse events.

Any adverse change from the infant's baseline condition (determined from screening evaluations conducted to confirm study eligibility) that occurs following the administration of the study vaccine will be considered an adverse event. This includes the occurrence of a new adverse event or the worsening of a baseline condition, whether or not considered related to the study vaccine. Intermittent conditions such as headaches may be present on Study Day 0 but may represent an adverse event if the intensity or duration of the event is worse than usual following receipt of study vaccine. Adverse events include but are not limited to: adverse changes from baseline that represent increases in toxicity grade according to the Toxicity Table (see protocol appendices), adverse changes in the general condition of the infant, signs and symptoms noted by the infant's caregiver, concomitant disease with onset or increased severity after study vaccine administration, and changes in laboratory safety parameters occurring after study vaccine administration.

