## Appendix C: Aeras Pediatric Toxicity Table

Note: This table is designed for grading the severity of adverse events in healthy children 3 months to 2 years of age.

| Local Site of Injection Symptoms            | Grade 1                                  | Grade 2                                                                              | Grade 3                                                   | Grade 4                                   |
|---------------------------------------------|------------------------------------------|--------------------------------------------------------------------------------------|-----------------------------------------------------------|-------------------------------------------|
| Injection site pain (pain without touching) | Minimal or no limitation of use of limb  | Limitation of use of limb OR greater than minimal interference with usual activities | Inability to perform usual activities                     | N/A                                       |
| Tenderness (pain when area is touched)      | Minimal or no limitation of use of limb  | Limitation of use of limb OR greater than minimal interference with usual activities | Inability to perform usual activities                     | N/A                                       |
| Erythema (Redness)*                         | Present, ≤ 1.0 cm in diameter            | > 1.0 cm to 2.5 cm in diameter                                                       | >2.5 cm in diameter                                       | Local or extensive exfoliative dermatitis |
| Induration or Edema                         | Present, ≤ 1.0 cm in diameter            | > 1.0 cm to 2.5 cm in diameter                                                       | >2.5 cm in diameter                                       | Local or extensive exfoliative dermatitis |
| Ulceration                                  | Minimal or no interference with activity | Some interference with activity not requiring medical intervention                   | Prevents daily activity and requires medical intervention | Requires hospitalization                  |

\* In addition to grading the local reaction at the greatest single diameter, record the measurement as a continuous variable.

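### Sections 3.5.2.1 and 5.3 disagree on when an abnormal laboratory value is an adverse event, and the Safety Cohort laboratory table, read literally, omits worsening from an abnormal baseline

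*Protocol*

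**What the plan says.** Three places in the protocol bear on a post-vaccination laboratory value.

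- Section 3.5.2.1 gives the site its reporting rule: "If the laboratory value is abnormal, it must be reported as an adverse event and repeated promptly to demonstrate resolution". It refers neither to the baseline value nor to a toxicity grade.
- Section 5.3 defines an adverse event against the infant's own baseline. It covers "the occurrence of a new adverse event or the worsening of a baseline condition", and its open list of examples includes "adverse changes from baseline that represent increases in toxicity grade according to the Toxicity Table". Conditions present before vaccination go into the medical history.
- Section 7.5.1 tabulates, for the Safety Cohort (Study Group 1), infants with "post-vaccination clinical laboratory values recorded as newly abnormal following study vaccination and meeting toxicity mild criteria (Grade 1) or above", at each post-vaccination time point and overall. The abstract, under the analysis of the primary objective, lists the same count among the key safety endpoints, as "newly abnormal post-vaccination laboratory values based on predefined neonatal toxicity criteria". The table actually supplied, Appendix C, is "designed for grading the severity of adverse events in healthy children 3 months to 2 years of age".

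Section 7.5.1 goes on: "Clinical laboratory abnormalities will also be reported as adverse events and will be included in the summary of adverse events". Of the adverse event summaries it says: "Additional summaries will include presentations by adverse event reporting period, by severity, and by relationship to study vaccine". Section 7.5.2 adds summary statistics for laboratory parameters, including change from the pre-vaccination value, by treatment group and study group.

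**The concern.** Safety is the primary objective, and section 7.5.1 makes adverse events the primary safety variable. Laboratory abnormalities feed into it. If one staff member follows 3.5.2.1 and another follows 5.3, the same pair of results is recorded differently, and the inconsistency is in the data before any analysis starts.

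The laboratory table has a separate weakness. An infant whose ALT goes from Grade 1 before vaccination to Grade 3 on Day 7 was already abnormal, so on the literal wording is not counted.

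Abnormal baselines are possible. The eligibility criteria in section 3.2.3 set no numeric chemistry or haematology limit. Section 3.5.2 withholds a blood draw only when a fingerprick haemoglobin, prompted by signs of anaemia, is below 9 g/dL. Appendix C grades 9.0 to 9.4 g/dL as Grade 1 at 3 to 6 months. An infant can therefore be sampled and enrolled with Grade 1 haemoglobin. Scheduled safety laboratory tests are planned only in this cohort, whose data the Safety Monitoring Committee reviews once its last infant completes Day 84.

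**Working it through.** **1. The protocol's own figures.** Section 7.6 gives an 80% chance of at least one event with a true rate of about 1% among 165 vaccinees: 1 − 0.99^165 = 0.8095. It gives more than 75% for a rate of 1 in 1000 among 1392: 1 − 0.999^1392 = 0.7516. Both reproduce.

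**2. The two recording rules.** Take six states for one parameter: normal, abnormal but below the Grade 1 cut-off, and Grades 1 to 4. The second state exists because, for example, Appendix C starts Grade 1 for ALT at 1.1 times the upper limit of normal. There are 6 × 6 = 36 baseline-to-post pairs.

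- Section 3.5.2.1 (post value abnormal): 5 abnormal post states × 6 baselines = 30 pairs are adverse events.
- Section 5.3, by its grade-increase criterion: 4 + 4 + 3 + 2 + 1 + 0 = 14 pairs.
- All 14 are among the 30, so the rules differ on 30 − 14 = 16 pairs.

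The 16 are not all of equal weight:

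| Baseline to post | Pairs | Comment |
|---|---|---|
| Graded to a lower grade or to abnormal-ungraded | 1 + 2 + 3 + 4 = 10 | Improved but still abnormal: a clear conflict |
| Same grade before and after | 4 | A conflict if the value is unchanged |
| Abnormal-ungraded before and after | 1 | A conflict if the value is unchanged |
| Normal to abnormal-ungraded | 1 | An adverse change that the open list in 5.3 could still cover |

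**3. The laboratory table.** Six pairs are a worsening from a graded baseline: 1 to 2, 1 to 3, 1 to 4, 2 to 3, 2 to 4 and 3 to 4. The 7.5.1 table counts 0 of 6. This holds whether newly abnormal means that the baseline was within the normal range or only that it was below Grade 1. The first reading counts 4 of the 14 grade increases, the second 8 of 14.

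**4. Where the six go instead.** All six are adverse events under both 3.5.2.1 and 5.3, so 7.5.1 sends them to the adverse event summary. Section 5.4 records Grade 2 as moderate and Grades 3 and 4 as severe. So 1 to 2 appears as moderate, and 1 to 3, 1 to 4, 2 to 3 and 2 to 4 as severe. Only 3 to 4 cannot be told apart by severity. The values also enter the change statistics of 7.5.2.

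**5. Size.** The protocol does not give the share of infants abnormal at baseline on a given parameter. Assume 10%, 20% or 30%, for illustration only. The vaccinees who could contribute a newly abnormal value on that parameter number 148, 132 or 115 (165 × 0.9, 0.8, 0.7, rounded down). The chance that this one table shows a 1% event is 1 − 0.99^n = 0.774, 0.735 or 0.685, against 0.810. Under 3.5.2.1, up to 165 × 0.10 = 16.5, 165 × 0.20 = 33 or 165 × 0.30 = 49.5 infants per arm could yield an adverse event from a baseline abnormality that had not worsened.

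**The case against.** The strongest reply is that the primary safety variable does capture the worsening. That is correct. A reader might infer that the Safety Cohort tables as a whole miss deterioration, or that the 7.5.1 laboratory table is the only laboratory evidence. The documents support neither: laboratory abnormalities enter the adverse event summary by study group, treatment group and severity, 7.5.2 reports change from baseline, and section 5.1.5 lets the Safety Monitoring Committee review laboratory data.

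A reader might also infer that the 80% detection chance is undermined. It is not. It concerns adverse events among all 165 vaccinees, and worsening from an abnormal baseline is an adverse event. Nor is every infant with an abnormal baseline lost from the table: judged per parameter, such an infant still counts for a new abnormality in another parameter.

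It can be said that 3.5.2.1, read together with 5.3, need not cover an unchanged value, and that grade increase is only one example in 5.3. The test in 5.3 is still an adverse change from baseline, and 3.5.2.1 contains no such condition. Any over-reporting should fall about equally on the two randomized arms, so it adds background noise and is not expected to bias the comparison.

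Finally, the statistical analysis plan may define newly abnormal and add a shift table. That weakens the second half of the point. It does not touch the first: an analysis plan can choose what to display, but not what the site was told to record.

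**Conclusion.** The point holds in two limited parts. First, 3.5.2.1 and 5.3 conflict on whether an abnormal laboratory value that has not worsened from an abnormal baseline is an adverse event. The conflict is clear for the ten improved-but-abnormal pairs and also applies to unchanged values, and it reaches the primary safety variable. Second, the 7.5.1 laboratory table, and the matching endpoint in the abstract, read literally omit all six worsenings from a graded baseline. That omission is confined to one table; the other outputs show the worsening, except that severity does not separate Grade 3 from Grade 4.

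The number of infants affected is unknown. The 10% to 30% shares are assumptions, and the figures built on them describe one parameter in one table. The change is worth making because it costs almost nothing and corrects both the recording rule and the table.

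**What to change.** - In 3.5.2.1, require an adverse event report when a value is abnormal and worse than the infant's own baseline, in line with 5.3. No worsening is lost: 5.3 alone already covers all 14 grade increases. The instruction on repeat testing is a separate matter and is not addressed here.
- In 7.5.1 and in the abstract, count infants with any increase in toxicity grade from their own baseline, per parameter, and add a shift table of baseline grade by worst post-vaccination grade, by treatment group. This also separates Grade 3 from Grade 4.
- In the same edit, reconcile the abstract's reference to neonatal criteria with the age range of Appendix C.

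The cost is wording in three places and one table. No new sampling is needed, because Safety Cohort baseline chemistry and blood counts are already collected within 14 days before randomization.
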